#### Data management

2.9.2

Data entry will be carried out using a validated electronic remote data capture system which complies with Food and Drug Administration (FDA) regulation 21 Code of Federal Regulation Part 11. Clinical data management will be performed in accordance with applicable GCP standards and data cleaning procedures to ensure the integrity of the data. All eCRF entries, corrections, and alterations must be made by the investigator or authorised site staff. Discrepancies in the data will be brought to the attention of the clinical team, and site staff, if necessary. Resolutions to these issues will be reflected in the database and an audit trail within the system will track all changes made to the data.

### Follow-up, study termination and withdrawal

2.10

All adverse events (AEs) or serious AEs reported or observed during the trial will be recorded on the eCRF. AEs resulting from concurrent illnesses, reactions to concurrent illnesses, reactions to concurrent medications, or progression of disease states must also be reported. All AEs will be followed to adequate resolution. All participants with AEs potentially related to the investigational products that are unresolved at the end of trial (or upon early withdrawal) must be followed up. The investigator will follow up with all participants experiencing AEs until resolution or stabilisation the event.

Participants may discontinue treatment or withdraw consent at any time for any reason, or if they withdraw consent due to not tolerating the trial treatment, not perceiving a benefit from the trial treatment, or preferring an alternative treatment. They may also discontinue from the trial if they experience a serious AE that in the investigator’s opinion require discontinuation from the trial, or develop a new medical condition that renders trial participation unsafe. Reasons for discontinuing trial treatment will be recorded.

### Statistical methods

2.11

The efficacy endpoints will be summarised using summary statistics in line with estimand strategies. Intercurrent events considered in this trial are treatment discontinuation, treatment noncompliance and initiation or adjustment of prohibited concomitant medication. The hypothetical strategy will be used to estimate the effects attributable to trial treatment without influence from prohibited medication and where the treatment is taken as intended. For the safety endpoints, the incidence of participants with AEs, adverse drug reactions, and serious AEs for the safety population will be summarised by treatment arms and exposure phases. The analysis will be exploratory in nature, and no formal hypothesis testing for confirmatory claims will be performed. Therefore, no primary endpoint has been selected, endpoints are not hierarchically ordered or weighted in the analysis and no adjustments for multiplicity will be applied. However, descriptive *p*-values will be provided with appropriate tests.

The full analysis set will be used for the efficacy analyses and the safety set for the safety analyses. Predefined subgroup analyses will be conducted for gender and age groups. Data collected in this trial will be presented using summary tables, patient data listings, and figures. Models such as the analysis of covariance (ANCOVA) and a mixed-effects model for repeated measures (MMRM) will also be explored to compare the efficacy parameters between the treatment groups. For the ANCOVA model, treatment will be included as factor, and baseline value will be included as continuous covariate. The MMRM will incorporate the Huber-White “Sandwich” standard error and will include visit, treatment, visit by treatment as factors, and baseline value (baseline value for the corresponding endpoint analysed) as a continuous covariate. Summary statistics will be provided for demographics, medical/surgical history, and physical examination at baseline and prior/concomitant medication. The homogeneity of treatment groups will be assessed through analysis of baseline characteristics. Additional details of all analyses and data reviews will be provided in the statistical analysis plan (SAP). A draught SAP will be developed prior to the randomisation of the first participant and will be finalised and signed off before the database is locked.

For categorical and ordinal variables, percentages will be calculated based on the number of participants in the corresponding analysis set and the number of participants with missing data will also be included. Additional details of handling of missing data or data not used after the occurrence of an intercurrent event by multiple imputation methods will be provided in the SAP.

Statistical analysis will be performed by an independent external service provider (Thermo Fisher Scientific, Wilmington, United States).

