### Study design

2.1

EGb COCOS is a prospective, multicentre, parallel-group, randomised, placebo-controlled, triple-blind (participants, clinicians, and data analysts) clinical trial. It aims to address the current lack of established treatment for cognitive impairment in PCS and to contribute to the understanding of the potential role of EGb 761®. The trial will be conducted at multiple sites in Germany, Poland, and Spain. The trial sites will be a mix of hospital and specialised research centres.

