### Randomization, treatment allocation

2.4

This is a triple-blind trial with all participants, site personnel, and data analysts blinded to treatment. All members of the clinical trial team, including investigators, site staff, outcome assessors, and data analysts, will be blinded to treatment assignments whilst the trial is in progress. Interventions will be supplied in identical packages and the tablets will be similar in colour, smell, taste, and appearance.

Participants will be randomised using automatic interactive response technology (IRT) by allocating multiple complete blocks to each site. Each participant number will be associated with treatment arms according to a random process.

Prospective participants will undergo a screening process prior to administration of the intervention (Figure 1). All participants who enter screening for the trial will receive a unique 5-digit participant identification number assigned by the IRT system, consisting of the 1-digit country code, the 2-digit centre code, and the 2-digit participant chronological number. If eligible for enrolment, the participant number will be associated with a medication number via the IRT system. Investigators, all site and sponsor personnel are unaware of the randomisation list.

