### Sample size calculation

2.8

Currently, there is very limited data on the use of EGb 761® in patients with cognitive impairment associated with PCS (Gebetsroither, 2024; Zifko et al., 2022). Therefore, the sample size was determined considering a small standardised mean difference (treatment effect size) according to Cohen’s d (Cohen, 1988).

A treatment effect size was reported as 0.52 for EGb 761® compared to placebo for cognition in a meta-analysis of dementia trials (Gauthier and Schlaefke, 2014). Because patients with dementia are more cognitively impaired and represent a more homogeneous population compared to patients with PCS, the treatment effect size is assumed to be smaller in PCS. To detect at least one significant outcome in the two cognitive domains memory and executive functioning assuming a treatment effect size of at least 0.25, a correlation of 0.3 to 0.4 between both domains (Napryeyenko et al., 2007; Ihl et al., 2011; Herrschaft et al., 2012; Nikolova et al., 2013), a statistical power of at least 80%, a local 2-sided significance level of 0.05, and a dropout rate of about 15%, 400 patients need to be randomised (R package rPowerSampleSize Version 1.0.2, R version 4.3–2 [2023-03-15]).

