The trial outcomes and assessments are easy to record, location-independent, and applicable across a diverse patient population. A narrative review of pharmacological studies evaluating treatment options for neuropsychiatric symptoms in PCS shows the current wide range of cognitive endpoints used (Lejay et al., 2023). No standardised approach has yet been established (see text Footnote 1). Notably, there is accumulating evidence of a discrepancy between subjective cognitive complaints and objective cognitive impairment in patients with PCS (Bland et al., 2024). Subjective complaints are more likely to be reported than objectively detected (Tarantini et al., 2025; Schild et al., 2023), highlighting the limitations of cognitive testing in this patient population. In the present trial, an exploratory trial design will be used that includes a range of validated cognitive endpoints (e.g., Digit span Forward and Backward, Verbal Fluency test, Symptom Burden Questionnaire for long COVID) (SBQ-LC, module “Memory, Thinking and Communication”). These have been chosen to cover both general cognitive impairment and COVID-19-associated cognitive impairment. Additionally, other symptoms linked to cognitive complaints and mediating the relationship between subjective cognitive symptoms and objective cognitive performance will be examined (Delgado-Alonso et al., 2025a; Denno et al., 2025). Post-exertional malaise (PEM) is a key feature of PCS and an important consideration for trial participants. One measure to limit the PEM risk was to restrict cognitive testing to the minimum required to achieve the trial objective. Therefore we restricted cognitive testing to those domains that have been reported to be affected most in PCS and to be most relevant for everyday life in PCS (Delgado-Alonso et al., 2022, Delgado-Alonso et al. 2025a, Panagea et al., 2025). Validated tests with available versions in Spanish, Polish, and German were selected for working memory (Digit Span Forward and Backward), verbal learning (California Verbal Learning Test), executive function (Trail-Making Test), verbal fluency, and sustained attention (d2 Test of Attention – Revised). Applying these tests as a fixed battery will allow to assess fatigability, a key feature of cognitive complaints in PCS that is poorly captured by other validated cognitive tests. Whilst this approach might miss treatment effects in cognitive domains not tested, such as visuospatial abilities or social cognition, the cognitive battery covers the domains most relevant in PCS.

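### Randomisation is blocked within site, but the listed ANCOVA and MMRM terms omit site and country: conservative, with a modest loss of efficiency if residual site variance is material

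*Protocol article*

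**What the plan says.** On allocation, the section on randomisation and treatment allocation describes an interactive response system "allocating multiple complete blocks to each site", in a 1:1 ratio. The word stratification is not used, but whole blocks reserved for each site make site a stratum in effect. Because sites lie within countries, country is balanced too. Study design adds: "The trial will be conducted at multiple sites in Germany, Poland, and Spain". The Discussion says of the cognitive battery: "Validated tests with available versions in Spanish, Polish, and German were selected".

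On analysis, Statistical methods gives the terms of two models. "For the ANCOVA model, treatment will be included as factor, and baseline value will be included as continuous covariate". The MMRM "will include visit, treatment, visit by treatment as factors, and baseline value" for the endpoint concerned. On its standard error: "The MMRM will incorporate the Huber-White “Sandwich” standard error". Neither list contains site or country.

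The same section presents the two models as examples to be explored, calls the analysis exploratory with descriptive p-values, and leaves further detail to the SAP. The Discussion promises adjustment for important known confounders only if the arms turn out unbalanced on them.

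**The concern.** Blocking within site forces the arms to be nearly equal at every site, so differences between sites largely cancel out of the treatment comparison. A model without site leaves those differences in the residual variance and so does not credit the balance. The estimate is more precise than its standard error says: intervals are too wide and tests are conservative.

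The article gives reasons why site could matter here. Tests are given in three languages by different raters, sites mix hospitals and specialised research centres, and the article itself says that practice effects come with repeated testing and that symptoms respond to expectation. The last two act after baseline, so adjusting for baseline need not remove them. CGI-I has no baseline value to adjust for at all.

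The clause on observed imbalance does not help, because a factor balanced by design will not normally trigger it. Since no endpoint is primary, readers will lean on estimates and intervals, so interval width has some weight.

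**Working it through.** **Inputs from the article.** Effect size: "assuming a treatment effect size of at least 0.25". For the two cognitive domains: "a correlation of 0.3 to 0.4 between both domains". Two-sided 0.05 per test; at least 80% power for at least one of the two; about 15% dropout; 400 randomised, so 400 × 0.85 = 340 evaluable, 170 per arm.

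**Assumptions.** The share v of residual variance (after baseline adjustment) that lies between sites, the number of sites and the block size are not given. I use v = 0.02 to 0.15, 20 or 40 sites, and blocks of 4.

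**Step 1: reproduce the sample size.** Power for at least one of two correlated two-sided z-tests reaches 80% with 167 per arm at correlation 0.4 (334 / 0.85 = 393 randomised) and 160 per arm at 0.3 (320 / 0.85 = 377). The stated 400 agrees with the first. With 170 per arm the power is 80.8% (0.4) to 82.3% (0.3), with no site term involved.

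**Step 2: ideal balance within site.** Take the total residual variance as 1, n = 170 per arm, k = √(1 − v), and m = 0.25 × √(170/2) = 2.305.
- A model without site reports variance 2/n; the true variance is (1 − v) × 2/n. Reported over true standard error = 1/k.
- True type I error without site = 2 × [1 − Φ(1.96/k)].
- Power without site = 1 − Φ((1.96 − m)/k); with site = 1 − Φ(1.96 − m/k).

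| v | SE ratio | Type I error, no site | Power, one endpoint: without / with site | Power, at least one of two (correlation 0.35): without / with site |
|---|---|---|---|---|
| 0.02 | 1.010 | 4.8% | 63.6% / 64.4% | 81.6% / 82.2% |
| 0.05 | 1.026 | 4.4% | 63.8% / 65.7% | 81.8% / 83.3% |
| 0.10 | 1.054 | 3.9% | 64.2% / 68.1% | 82.1% / 85.1% |
| 0.15 | 1.085 | 3.4% | 64.6% / 70.5% | 82.4% / 86.9% |

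These are upper limits on the gain: balance is perfect and the site terms cost nothing.

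**Step 3: with dropout and incomplete blocks.** Simulation of 400 randomised, 15% random dropout, site as unpooled fixed effects, 4,000 runs per setting (Monte Carlo standard error of a power of 0.64: √(0.64 × 0.36 / 4,000) = 0.8 points).

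| v | Sites | Type I error: without / with site | Power: without / with site |
|---|---|---|---|
| 0 | 20 | 5.1% / 5.0% | 62.7% / 61.8% |
| 0 | 40 | 4.6% / 4.4% | 62.4% / 61.2% |
| 0.02 | 20 | 4.7% / 5.1% | 63.1% / 63.3% |
| 0.02 | 40 | 4.7% / 4.8% | 63.8% / 62.9% |
| 0.05 | 20 | 4.6% / 5.1% | 63.5% / 64.2% |
| 0.05 | 40 | 4.6% / 5.2% | 62.6% / 64.0% |
| 0.10 | 20 | 4.1% / 5.3% | 63.3% / 66.7% |
| 0.10 | 40 | 3.9% / 4.9% | 64.0% / 66.7% |

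At v = 0.10 with 20 sites and no effect, the mean reported standard error was 0.1081 against an empirical SD of 0.1038, a ratio of 1.041 rather than the ideal 1.054.

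A separate simulation of the same design put the gain at about 2 points at v = 0.05, 2 to 3 at 0.10 and 5 at 0.15. Another, with 40 sites of 10, gave a standard error excess of about 1.5 to 3% for v = 0.05 to 0.10, and a loss from fixed site terms at v = 0 of 63.2 − 61.3 = 1.9 points. The runs agree on direction and rough size.

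**The case against.** The strongest reply is that this is a condensed article describing an exploratory analysis. Its models are offered as examples, detail is left to the SAP, and nothing bars a further term. That stands: the listed terms can be compared with the randomisation, but they should not be read as a settled final model.

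Next, the harm depends on a quantity that the documents do not give. Baseline adjustment removes much of any stable level difference between language versions and raters, all raters are trained, and many endpoints are self-ratings. That also stands. A reader might infer that precision is lost on every endpoint; where the residual site share is 0 to 0.02, essentially nothing is lost.

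The remedy can also cost power. With many small sites, unpooled fixed effects and negligible site variance, the runs above show a loss of about 1 point, and 1.9 in one of them. This bears on how site is modelled rather than on whether the stratum is considered.

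Finally, the article does not state the clustering unit of the sandwich estimator. Clustered by participant, the usual reading, it does not credit the balance within site; clustered by site, it could. This concerns the MMRM only.

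**Conclusion.** The mismatch is real and its effect is minor. Allocation is blocked by site, and the listed ANCOVA and MMRM terms include neither site nor country. If the residual between-site share is 0.05 to 0.15 (an assumption), standard errors are up to about 3 to 8% too large, type I error is about 3.4 to 4.4% instead of 5%, and about 2 to 5 points of per-endpoint power are forgone at an effect size of 0.25 with 170 per arm. Dropout shrinks these figures: the tabulated runs at 0.05 show gains of only about 1 point.

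Two stronger readings are not supported. A reader might infer that omitting site biases the estimate or inflates false positives; the error runs the other way, towards conservative tests. A reader might also infer that the trial is underpowered; the planned 80% for at least one of two domains is met without a site term (80.8 to 82.3%). What is lost is precision that the design already offers.

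**What to change.** Prespecify in the SAP, for both the ANCOVA and the MMRM, a term for the randomisation stratum: either site as a factor with small sites pooled within country, by a pooling rule fixed before unblinding, or a random site effect. Use country alone if sites prove many and small or a model does not converge; country recovers only the between-country part of the variance. State the clustering unit of the sandwich standard error at the same time.

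The change needs no new data. It costs some degrees of freedom: unpooled fixed effects use one fewer than the number of sites, for example 19 with 20 sites or 39 with 40. About 1 point of power is lost if there are many small sites, they are left unpooled as fixed effects and site variance is negligible. Pooling or a random effect is meant to limit that loss. The article has the SAP finalised only before database lock, so there is a natural place for the change.

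### The listed MMRM gives baseline one common slope at Week 6 and Week 12; if the true slopes differ, Week 12 loses a little precision and, with direct fitting to incomplete data and arm-dependent dropout, picks up a small bias that a baseline-by-visit term would remove

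*Protocol article*

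**What the plan says.** Section 2.11 (Statistical methods) of the protocol article names two models that "will also be explored to compare the efficacy parameters between the treatment groups". The first is an ANCOVA: "For the ANCOVA model, treatment will be included as factor, and baseline value will be included as continuous covariate". The second is an MMRM with Huber-White standard errors, which "will include visit, treatment, visit by treatment as factors, and baseline value (baseline value for the corresponding endpoint analysed) as a continuous covariate". One interaction is spelled out, visit by treatment; baseline by visit is not among the terms. The two post-baseline visits are Week 6 and Week 12 (section 2.7).

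Three other statements bear on the point. Section 2.8 plans for "a dropout rate of about 15" per cent and an effect size of at least 0.25. Section 2.11 leaves to the SAP "Additional details of handling of missing data or data not used after the occurrence of an intercurrent event by multiple imputation methods". It also says that "no formal hypothesis testing for confirmatory claims will be performed" and names no primary endpoint. The SAP is not shown.

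**The concern.** A single baseline covariate in a repeated-measures model assumes that a one-point difference at baseline carries the same expected difference to Week 6 as to Week 12. Baseline often predicts a later visit less well than an earlier one. If that is so here, the fitted slope is a compromise weighted towards Week 6, where residual noise is smaller, and Week 12 is adjusted with a slope that does not fit it.

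Two things would be at stake. The first is some precision at Week 12. The second is bias. If those who stay have a different mean baseline in the two arms, the wrong slope no longer cancels between arms. Such dropout, depending on baseline alone, is missing at random, which is the situation an MMRM is meant to handle. The sandwich estimator repairs the standard error under misspecification but leaves the point estimate where it is.

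**Working it through.** **Inputs from the protocol article.** Model terms (2.11); visits at Week 6 and Week 12 (2.7); effect 0.25 SD, correlation 0.3 to 0.4 between the two domains, dropout about 15%, 400 randomised (2.8).

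**Assumed inputs (not in the article).** Scores with unit variance; baseline slopes b6 and b12, equal to the baseline correlations with Week 6 and Week 12; correlation r between the two visits; 15% dropout in each arm after Week 6, logistic in baseline only.

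**The plan's own figure.** The power for at least one significant result of two is 1 − P(|Z1| < 1.96 and |Z2| < 1.96), each Z with mean 0.25/√(2/n). This needs 160 per arm at correlation 0.3 and 167 at 0.4. With dropout that is 320/0.85 = 377 and 334/0.85 = 393 randomised. With 170 evaluable per arm (400 less 15%), power is 82.3% or 80.8%. The 400 reproduces. It does not depend on the MMRM; only the 0.25 is used below, as a yardstick.

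**Step 1: the common slope.** Worked for b6 = 0.75, b12 = 0.60, r = 0.75.
- Residual variances: 1 − 0.75² = 0.4375 and 1 − 0.60² = 0.64. Residual covariance: 0.75 − 0.75 × 0.60 = 0.30.
- GLS weights are proportional to 0.64 − 0.30 = 0.34 (Week 6) and 0.4375 − 0.30 = 0.1375 (Week 12), that is 71% and 29%.
- Common slope b = 0.712 × 0.75 + 0.288 × 0.60 = 0.707.

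**Step 2: precision with complete data.** The Week 12 residual variance rises by (b12 − b)²/0.64 = 0.107²/0.64 = 1.8%, and the standard error by √1.018 − 1 = 0.9%.

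**Step 3: bias with direct fitting to incomplete data.** Let m be the mean baseline of those who stay in an arm, relative to all randomised. With Week 6 complete, the likelihood-based Week 12 mean in that arm is off by m × k, where k = (b12 − b) − γ(b6 − b) and γ is the residual covariance over the Week 6 residual variance. The treatment contrast is off by k times the difference in m between arms.
- γ = 0.30/0.4375 = 0.686, so k = −0.107 − 0.686 × 0.043 = −0.136.
- If dropout odds change 2.7-fold per SD of baseline (log-odds slope 1), integrating the dropout curve over a standard normal baseline gives |m| = 0.133.
- Dependence in one arm only: 0.133 × 0.136 = 0.018 SD. Opposite dependence: 2 × 0.018 = 0.036 SD.

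**Step 4: range of assumptions.** The same formulas, beside simulation. The standard-error column uses 1,500 trials of N = 400 with dropout unrelated to baseline. The bias columns use very large simulated data sets and show the bias of the common-slope fit in excess of the by-visit fit. Log-odds slope is 1 throughout.

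| b6 / b12 (r) | SE loss, formula | SE loss, simulated | One-arm bias, formula / simulated | Opposite bias, formula / simulated |
|---|---|---|---|---|
| 0.70 / 0.70 (0.70) | 0 | 0 | 0 / 0.000 | 0 / 0.000 |
| 0.70 / 0.65 (0.70) | 0.1% | not run | 0.005 / 0.005 | 0.010 / 0.011 |
| 0.70 / 0.60 (0.70) | 0.3% | 0.3% | 0.011 / 0.011 | 0.022 / 0.023 |
| 0.75 / 0.60 (0.75) | 0.9% | not run | 0.018 / 0.019 | 0.036 / 0.037 |
| 0.70 / 0.50 (0.60) | 1.1% | 0.6% | 0.022 / 0.023 | 0.044 / 0.045 |
| 0.80 / 0.50 (0.60) | 3.5% | 3.3% | 0.036 / 0.036 | 0.072 / 0.073 |

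A second set of simulations used slopes 0.80/0.70, 0.75/0.60 and 0.70/0.50, dropout of 12% to 16%, and odds rising 1.6- to 2.7-fold per SD. It gave 0.006 to 0.026 SD for one arm and 0.025 to 0.051 SD for opposite patterns.

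**Step 5: when it vanishes.** If b6 = b12, then b equals both and k = 0. If dropout depends on baseline equally in both arms, the two m cancel; simulated bias was zero within error. With baseline-by-visit in the model, simulated Week 12 bias was at most 0.004 SD in absolute value, which is simulation error. With complete data, randomisation makes the expected baseline difference zero, so only the cost in Step 2 remains.

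**The case against.** The case against is substantial, and much of it stands.

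- **Are the slopes different?** A reader might infer from section 2.5, which mentions fluctuation, spontaneous improvement and practice effects, that they must be. The article does not support that. A general practice effect or improvement shifts the visit means, which the visit term absorbs, and fluctuation can weaken both correlations alike. The difference remains an assumption.
- **Does the MMRM carry the missing data?** A reader might infer that the Week 12 estimate is therefore biased. The article assigns the "handling of missing data or data not used after the occurrence of an intercurrent event" to multiple imputation. If values are first properly imputed with visit-specific baseline slopes, the common-slope MMRM is unbiased and only a small precision cost is left. The bias figures apply to direct fitting on incomplete data, which the article neither states nor rules out.
- **Is it large?** At N = 400 the simulated Week 12 standard error was about 0.08 to 0.095 SD, so a bias of 0.02 SD is roughly a quarter of it. The larger values need opposite dropout patterns, which nothing in the article predicts.
- **Does disagreement with the ANCOVA prove a fault?** No. With complete data both are unbiased. They differ by chance baseline imbalance times the slope error, about 0.10 × 0.107 = 0.01 SD in the worked example.
- **Is it exploratory detail for the SAP?** The models are exploratory, and an ANCOVA fitted at Week 12 has its own slope. But section 2.11 lists the MMRM terms explicitly, so the common slope is a stated choice that an SAP may inherit. Exploratory status does not remove bias from an estimate.

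**Conclusion.** The point holds conditionally. As listed, the MMRM imposes one baseline slope on both visits. If the true slopes differ, Week 12 precision falls by about 0 to 0.6% of the standard error in the moderate settings simulated (the complete-data formula gives up to about 1%) and by about 3% in an extreme one. If, in addition, the model is fitted directly to incomplete data and dropout depends on baseline differently by arm, the Week 12 contrast is biased under missing-at-random. The bias is about 0.006 to 0.026 SD for dependence in one arm (2% to 10% of 0.25). For opposite patterns it is about 0.02 to 0.05 SD (8% to 20%), less when the slopes are close, and about 0.07 SD (28%) in the extreme case, where one-arm dependence also reaches about 0.036 SD. Its sign depends on the dropout pattern.

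Every correlation and dropout slope here is assumed. The article does not show that the Week 12 effect will be biased, and the sample size is unaffected. This is an inexpensive improvement to a stated model, not a demonstrated error in the trial's results.

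**What to change.** List the MMRM terms as visit, treatment, visit by treatment, baseline and baseline by visit, with an unstructured covariance. Let any imputation model use visit-specific baseline slopes too, so that the common-slope assumption does not return through the imputed values. With complete data, the Week 12 MMRM contrast then equals the Week 12 ANCOVA estimate, and the two planned models agree.

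The cost is one model term and one degree of freedom, with about 340 (400 × 0.85) to 400 participants contributing. Section 2.11 has the SAP finalised before database lock, so the change can be made there.
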